# NIPU: a randomised, open-label, phase II study evaluating nivolumab and ipilimumab combined with UV1 vaccination as second line treatment in patients with malignant mesothelioma

**DOI:** 10.1186/s12967-021-02905-3

**Published:** 2021-05-31

**Keywords:** Malignant pleural mesothelioma, Telomerase vaccine, Immunotherapy, hTERT, Nivolumab, Ipilimumab, Biomarker, Immune response

## Abstract

**Background:**

Malignant pleural mesothelioma (MPM) is a rare and aggressive tumour. For patients with inoperable disease, few treatment options are available after first line chemotherapy. The combination of ipilimumab and nivolumab has recently shown increased survival compared to standard chemotherapy, but most patients do not respond and improvements are called for. Telomerase is expressed in mesothelioma cells, but only sparsely in normal tissues and is therefore an attractive target for therapeutic vaccination. Vaccination against telomerase is tolerable and has shown to induce immune responses associated with increased survival in other cancer types. There is a well-founded scientific rationale for the combination of a telomerase vaccine and checkpoint inhibition to improve treatment response in MPM patients.

**Methods:**

NIPU is a randomized, multi-centre, open-label, phase II study comparing the efficacy and safety of nivolumab and ipilimumab with or without telomerase vaccine in patients with inoperable malignant pleural mesothelioma after first-line platinum-based chemotherapy. Participants (n = 118) are randomized 1:1 into two treatment arms. All participants receive treatment with nivolumab (240 mg every 2 weeks) and ipilimumab (1 mg/kg every 6 weeks) until disease progression, unacceptable toxicity or for a maximum of 2 years. Patients randomised to the experimental arm receive 8 intradermal injections of UV1 vaccine during the first three months of treatment. Tumour tissue, blood, urine, faeces and imaging will be collected for biomarker analyses and exploration of mechanisms for response and resistance to therapy.

**Discussion:**

Checkpoint inhibition is used for treatment of mesothelioma, but many patients still do not respond. Increasing therapy response to immunotherapy is an important goal. Possible approaches include combination with chemotherapy, radiotherapy, targeted therapy and other immunotherapeutic agents. Predictive biomarkers are necessary to ensure optimal treatment for each patient and to prevent unnecessary side effects. This trial seeks to improve treatment response by combining checkpoint inhibition with a telomerase vaccine and also to explore mechanisms for treatment response and resistance. Knowledge gained in the NIPU study may be transferred to the first line setting and to other cancers with limited benefit from immunotherapy.

*Trial registration*: ClinicalTrials.gov: NCT04300244, registered March 8th, 2020, https://clinicaltrials.gov/ct2/show/NCT04300244?term=NIPU&draw=2&rank=1.

## Background

Malignant pleural mesothelioma (MPM) is a rare and aggressive tumour originating from the cells lining the mesothelial surface in the lungs. Median overall survival (OS) is ~ 1 year [1]. Asbestos exposure is linked to development of the disease [2]. Most patients diagnosed with malignant pleural mesothelioma are inoperable and have been treated with cisplatin in combination with pemetrexed which has been the standard of care first-line therapy worldwide since 2003.

Intra-tumour infiltration of CD8+ T cells is associated with improved outcome in MPM [3] and a high expression of PD-L1 is associated with poor prognosis in this group of patients [4]. Monotherapy using pembrolizumab, nivolumab or avelumab has demonstrated a response rate of 9.3–20% [5–7]. The only phase 3 trial combining PD-1 and CTLA4 inhibition (Checkmate 743) showed an increased median survival from 14.1 to 18.1 months, and a duration of response of 11.0 vs 6.7 months in the combination arm vs the chemotherapy arm, respectively [8]. However, almost all the benefit was seen in patients with biphasic or sarcomatoid disease, whereas those with epithelioid disease did not benefit significantly. Grade 3 or 4 toxicity with the combination has been found in 17–34% of patients and has generally been manageable. The most common toxicities have been from the skin, gastrointestinal tract, hormone system and infusion reactions [8]. Based on these results, the FDA approved the combination of ipilimumab and nivolumab in the first line setting in October 2020.

Although these results are encouraging, the response rates seen are moderate compared to what has been documented for the combination of checkpoint inhibitors in other cancer diseases, indicating that checkpoint inhibitors alone are not enough to trigger an activation of an immune response against MPM. MPM is often found to be immunologically ‘cold’ tumours (lacking immune cell infiltration), but previous studies have indicated that treatment can increase immune cell infiltration in such cold MPM tumours by oncolytic virus [9]. Combining checkpoint inhibition with a treatment that can increase lymphocyte infiltration in the tumour could increase the response rates. One such approach is to use a vaccine aiming to activate an immune response directed against tumour-related antigens, and to combine the vaccine with checkpoint inhibitors.

UV1 is a therapeutic cancer vaccine directed against telomerase produced by Ultimovacs ASA. Telomerase maintains telomere length in dividing cells and is considered essential for tumour growth. It is expressed at high levels in more than 85% of human tumours, but only sparsely in normal tissues [10]. Since telomerase is an essential enzyme and universally expressed by most tumour cells, it represents a unique cancer antigen as a basis for immunotherapy.

In the NIPU-trial, UV1 will be tested in combination with ipilimumab and nivolumab to assess its ability to increase the treatment response in patients with MPM in the second line setting. This study was designed prior to the positive results of the CheckMate 743 trial, and may also inform the potential for UV1 vaccination in the first line setting.

## Methods/design

Oslo University Hospital is sponsor of the study. We have established collaborations for patient recruitment with cancer centres in Australia, Denmark, Sweden and Spain. University of Western Australia is sponsor for the study in Australia. Patient recruitment started in June 2020 and is expected to finish by May 2022. Initiation of the trial was postponed due to the COVID-19 pandemic. By March 2021, patients are included in Norway, Australia and Denmark.

### Objectives

#### Primary objective

To evaluate and compare the efficacy of nivolumab and ipilimumab with or without UV1-vaccine in patients with inoperable malignant pleural mesothelioma progressing after first-line platinum-based chemotherapy. The primary end point will be progression free survival (PFS) evaluated by modified response evaluation criteria in solid tumours (mRECIST) [11, 12] as determined by blinded, independent central review (BICR).

#### Secondary objectives

To compare overall survival (OS), objective response rate (ORR), disease control rate (DCR), time to response (TTR) and duration of response (DOR) according to Response Evaluation Criteria in Solid Tumours, version 1.1 (Modified RECIST), in patients who receive nivolumab and ipilimumab with patients who receive nivolumab and ipilimumab in combination with UV1.To evaluate changes from baseline in patient-reported outcomes (PROs) of lung cancer symptoms, patient functioning, and health-related quality of life (HRQoL) in patients who receive nivolumab and ipilimumab compared to patients who receive nivolumab and ipilimumab in combination with UV1.To determine tolerability in patients who receive nivolumab and ipilimumab compared to patients who receive nivolumab and ipilimumab in combination with UV1.

#### Exploratory/translational objectives

To characterise the TCR repertoire in patients receiving checkpoint inhibition alone compared with in combination with UV1 vaccination.To evaluate tumour mutational burden (TMB) as a predictive biomarker of response to therapy.To assess any difference in immune cell infiltration in tumour pre- and post-treatment with checkpoint inhibition alone or with UV1 vaccination.To assess vaccine-specific T-cell response in the blood cells of patients treated with UV1 vaccination.To assess any correlation between the microbial composition in faeces and treatment response.Evaluate dual-time PET as a predictive marker of therapy response and assess the ability of dual-time PET to distinguish between different cell types in the tumour.

### Study design

This is a randomized, multi-centre, open-label, proof of concept study comparing the efficacy and safety of nivolumab and ipilimumab with or without UV1 in patients with inoperable malignant pleural mesothelioma after first-line platinum-based chemotherapy.

The patients (n = 118) will be randomized 1:1 into two treatment arms (see Fig. 1):ANivolumab and ipilimumab plus 8 UV1 vaccinations.BNivolumab and ipilimumab alone.

**Fig. 1 Fig1:**
[figure not shown]
Study design of the NIPU trial. Patients with MPM and progression after first line platinum-based chemotherapy are randomised (1:1) to ipilimumab and nivolumab alone or in combination with UV1 vaccine.

Treatment will be continued until disease progression, unacceptable toxicity or for a maximum of 2 years. Because of the potential for pseudo progression/tumour immune infiltration, this study will allow patients to remain on study treatment after apparent radiographic progression, provided the risk/benefit ratio is judged to be favourable.

Biological material will be sampled, and translational explorative analyses will be performed to identify biomarkers and reveal mechanisms of response and resistance

#### Dosage

Nivolumab: 240 mg every 2 weeks for 2 years until progression or unacceptable toxicity.Ipilimumab: 1 mg/kg every 6 weeks for 2 years until progression or unacceptable toxicity.UV1 vaccination (arm A only): 8 intradermal injections with 300 μg UV1 and 75 μg GM-CSF (sargramostim) during the first 13 weeks. The first 3 UV1 vaccinations will begiven in week 1, one in week 2, followed by four UV1 vaccinations throughout the following 11 weeks, totalling eight vaccinations. The first three vaccinations of UV1 will be given prior to the first infusion of nivolumab and ipilimumab.

Overview of the study procedures and treatment can be found in Table 1.

**Table 1 Tab1:** Overview of study treatment and procedures

Weeks	Study period									
							Up to 2 years	EOT	Q3M safety FU	Q3M survival FU
	–4–0	1	2	3–5	6–7	12	Q6W			
Enrolment										
Informed consent	×									
Randomisation	×									
Treatment arm A										
UV1		× × ×	×	× ×	×	×				
Nivolumab Q2W			×	×	×	× × ×	× × ×			
Ipilimumb Q6W			×		×	×	×			
Treatment arm B										
Nivolumab Q2W		×		× ×	×	× × ×	× × ×			
Ipilimumb Q6W		×			×	×	×			
Procedures										
CT	×				×	×	×	×	×	
Dual-time PET	×				×			×		
Biopsy	×				×			×		
Study blood samples	×				×			×	×	
HR-QoL	×				×	×	×	×		
Clinical e×amination Q2W	×		×	×	×	× × ×	× × ×	×		
AE/SAE Q2W	×		×	×	×	× × ×	× × ×	×		
Disease status/survival									×	×

In summary, UV1 is safe alone and in combination with checkpoint inhibitors and trials in other cancers show that UV1 induces vaccine-specific immune response associated with survival.

### Patient selection

Selected inclusion and exclusion criteria are shown in Table 2.

**Table 2 Tab2:** Selected inclusion and exclusion criteria

Selected inclusion criteria	Selected exclusion criteria
1. Histologically and/or cytologically confirmed MPM	1. Disease suitable for curative surgery
2. Unresectable disease, not candidate for curative surgery	2. Previous treatment with a PD1 or PD-L1 inhibitor
3. Measurable disease, defined as at least one lesion (CT or MRI) that is suitable for repeated assessment	3. Non-pleural mesothelioma e.g. mesothelioma arising in other organs
4. Available unstained archived tumour tissue sample	4. Active second malignancy other than non-melanoma skin cancer or cervical carcinoma in situ
5. Previously treated with at least one line of platinum doublet	5. Symptomatic or uncontrolled brain metastases requiring concurrent treatment
6. ECOG performance status of 0–1	6. Known history of leptomeningeal carcinomatosis
7. Willing to provide archived tumour tissue and blood samples for research	7. Active or prior documented autoimmune or inflammatory disorders
8. Adequate organ function	8. History of primary immunodeficiency
9. Age ≥ 18 years	9. History of allogeneic organ transplant
	10. Uncontrolled intercurrent illness
	11. Active infection

### Safety measures

#### Handling of toxicities

Administration of study treatment will be performed in a setting with emergency medical facilities and staff who are trained to monitor for and respond to medical emergencies. All adverse events and serious adverse events will be recorded during the trial and for up to 30 days after the last dose of study drug or until the initiation of another anti-cancer therapy, whichever occurs first. After this period, investigators should report serious adverse events and adverse events of special interest that are believed to be related to prior treatment with study drug. Events will be graded according to NCI CTCAE v5.0.

#### Dose reduction considerations (selected points)

Dose reduction of nivolumab or ipilimumab is not permitted, apart from changing the dosing intervals for ipilimumab to every 12th week.For any concomitant conditions already apparent at baseline, the dose modifications will apply according to the corresponding shift in toxicity grade, if the investigator feels it is appropriate. For example, if a patient has grade 1 asthenia at baseline that increases to grade 2 during treatment, this will be considered a shift of one grade and treated as grade 1 toxicity for dose-modification purposes.When several toxicities with different grades of severity occur at the same time, the dose modifications should be according to the highest grade observed.If, in the opinion of the investigator, a toxicity is considered to be due to some component of the treatment leading to a dose delay, the other component(s) may be administered if there is no contraindication.If a patient experiences a grade 3 or 4 adverse event considered probably related to ipilimumab, the ipilimumab dosing interval should be extended to every 12 weeks. The ipilimumab dose should be kept at 1mg/kg.Patients may temporarily suspend study treatment with nivolumab/ipilimumab if they experience an adverse event that requires a dose to be held.If nivolumab is held because of adverse events for > 42 days (6 weeks), the patient will be discontinued from nivolumab treatment.If ipilimumab is held because of adverse events for > 126 days (18 weeks), the patient will be discontinued from nivolumab treatment.If the patient is likely to benefit from resuming nivolumab/ipilimumab after a longer hold than allowed (6 or 18 weeks), the study drug may be restarted with the approval of the Sponsor. If a patient must be tapered off steroids used to treat adverse events, nivolumab may be held for > 42 days until steroids are discontinued or reduced to prednisone dose equivalent ≤ 10 mg/day.The treating physician may use discretion in modifying or accelerating the dose modification guidelines described depending on the severity of toxicity and an assessment of the risk versus benefit for the patient, with the goal of maximizing patient compliance and access to supportive care.Dose modification of GM-CSF (sargramostim) or UV1 is not allowed in this study. If ipilimumab and nivolumab are withheld during the study treatment period, UV1 vaccination must also be withheld. UV1 vaccinations will only be reintroduced if both ipilimumab and nivolumab are reintroduced.UV1 vaccination and/or ipilimumab and nivolumab not administered will not be replaced during the study treatment period.

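### The stopping rule for an ipilimumab hold of more than 18 weeks names nivolumab, not ipilimumab, as the drug to discontinue

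*Protocol article*

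**What the plan says.** The section on dose reduction considerations gives two hold limits in consecutive sentences. For nivolumab: "If nivolumab is held because of adverse events for > 42 days (6 weeks), the patient will be discontinued from nivolumab treatment". For ipilimumab: "If ipilimumab is held because of adverse events for > 126 days (18 weeks), the patient will be discontinued from nivolumab treatment". The triggers differ; the consequence is the same.

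Three other rules in that section bear on how to read the second sentence:

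- Restart with sponsor approval, for a patient "likely to benefit from resuming nivolumab/ipilimumab after a longer hold than allowed (6 or 18 weeks), the study drug may be restarted".
- Separate handling of components: when a toxicity attributed to one component leads to a dose delay, "the other component(s) may be administered if there is no contraindication".
- Steroid taper: "nivolumab may be held for > 42 days until steroids are discontinued" or reduced to a low dose.

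The Dosage section gives nivolumab "every 2 weeks for 2 years until progression or unacceptable toxicity" and ipilimumab "every 6 weeks for 2 years until progression or unacceptable toxicity".

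**The concern.** A rule triggered by a long ipilimumab hold would be expected to end ipilimumab. As printed it ends nivolumab, and no other sentence stops ipilimumab because of the length of a hold. Ipilimumab still stops at progression, unacceptable toxicity or 2 years, but the 18-week limit has no stated consequence for the drug it limits.

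Both drugs are the backbone of both arms, so the rule applies to every randomised patient. Followed literally, a patient who tolerates nivolumab while ipilimumab is held beyond 18 weeks would have to stop nivolumab. If ipilimumab were then resumed, the patient would be on ipilimumab without nivolumab, which is neither arm's regimen. What is at stake is patient treatment and consistent dosing across sites, not the statistical design.

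**Working it through.** **The stated limits.** 42 days / 7 = 6 weeks and 126 days / 7 = 18 weeks. Both conversions are right, so only the named drug is in question.

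**The sentences side by side.**

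| Rule | Drug held | Limit | Drug stopped |
|---|---|---|---|
| First hold rule | nivolumab | 42 days (6 weeks) | nivolumab |
| Second hold rule, as printed | ipilimumab | 126 days (18 weeks) | nivolumab |
| Restart rule | nivolumab / ipilimumab | 6 or 18 weeks | implies each drug stops at its own limit |

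The restart rule is the strongest evidence. It lets the sponsor lift a stop for either drug once its permitted hold is exceeded. Under the printed second rule there is no ipilimumab stop to lift.

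**Dosing intervals (supporting only).** With nivolumab every 14 days, 42 / 14 = 3 intervals. With ipilimumab every 42 days, 126 / 42 = 3 intervals. Each limit is three standard intervals of the drug being held, as expected if the two sentences were written as a parallel pair. For a patient moved to 12-weekly ipilimumab (84 days) the ratio is 126 / 84 = 1.5, so the pattern holds only for the standard schedule.

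**Upper bound on lost nivolumab for one patient.** Assumptions: arm B calendar (both drugs start in week 1), ipilimumab held after its first dose, nivolumab tolerated throughout and otherwise given for the full 2 years.

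- Planned nivolumab doses: 104 weeks / 2 = 52.
- Hold counted from the last ipilimumab dose (week 1): the limit is reached 18 weeks after start, in week 19. Doses at 0, 2, …, 18 weeks: 18 / 2 + 1 = 10 given. Lost: 52 − 10 = 42.
- Hold counted from the first missed dose (week 7, 6 weeks after start): the limit is reached 6 + 18 = 24 weeks after start, in week 25. Doses at 0, 2, …, 24 weeks: 24 / 2 + 1 = 13 given. Lost: 52 − 13 = 39.

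Later holds remove fewer doses. The article gives no figure for how many patients would be held this long, so no trial-level total can be computed.

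**The case against.** The best counter-argument is that this is an editorial slip in a published summary. The section is headed as a selection of points. Recruitment began in June 2020 and the article appeared in May 2021, so sites were already treating patients under a full protocol that is not shown. If that protocol has the right wording, no patient was affected. This stands as a limit on what can be claimed about harm, and it is why any action at sites depends on checking the full protocol. It does not excuse the sentence: condensing explains what is left out, not a rule that names the wrong drug.

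Some of the supporting evidence is also open to challenge:

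- The steroid exception concerns only nivolumab's 42-day limit and fits either reading. It adds little.
- The three-interval pattern confirms the trigger more than the consequence, and fails for 12-weekly ipilimumab.
- The rule on other components is permissive and concerns a delay, so it does not strictly forbid a later cap. The protocol does link drugs elsewhere: UV1 returns only if both checkpoint inhibitors do. A deliberate linked stop is therefore conceivable. However, no rationale is given, such a rule would ordinarily stop both drugs, and ipilimumab would still lack the stop that the restart rule assumes.

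The dose-loss figures are an extreme case. If the 69% and 51% progression figures in the Statistical analyses section are read as 12-month risks with constant hazard (an assumption), the progression-free shares at 2 years are 0.31² ≈ 10% and 0.49² ≈ 24%. Few patients would complete 52 doses, although some treatment beyond apparent progression is allowed. The figures bound the effect; they do not estimate it.

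Finally, sponsor-approved restart and physician discretion would in practice rescue many affected patients. They soften the rule without correcting it.

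**Conclusion.** The point holds. The sentence is wrong as written: it stops the drug that was not held and leaves the held drug without a hold-length limit, contrary to what the restart rule in the same section presupposes. No other part of the article corrects it. A carry-over from the preceding sentence is by far the likeliest cause, and even a deliberate cross-drug rule would need rewording.

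The effect is on treatment instructions in both arms. For one patient the loss is at most 42 of 52 nivolumab doses, or 39 on the other way of counting the hold, under the assumptions stated. The number of patients is unknown, and whether any were affected depends on the full protocol. The primary endpoint, the 69 required events, power and alpha do not change. It should be fixed because the correction is trivial and the rule governs a backbone drug.

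**What to change.** End the sentence with discontinuation of ipilimumab in place of nivolumab. If the intention was to stop both drugs after a long ipilimumab hold, name both.

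Then compare with the full protocol. If it is already correct there, only the article needs correcting. If it repeats the wording, send sites a clarification and list any patient whose nivolumab was stopped under this rule.

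The cost is one word and a document check, with a site letter and a short patient listing only if the full protocol has the same error.

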
#### Independent data monitoring

An independent data monitoring committee (IDMC) has pre-planned assessment of the safety of the trial 4 and 13 weeks after the first 6 and 14 patients have started treatment. All the IDMC assessments has been successfully completed.

### Sample collection/biobanking

An extensive research program will be conducted. The patient informed consent form will allow for performing biomarker analyses, immunological studies, gene profiling and studies of tumour evolution/heterogeneity during treatment, as well as comparison with data/material from other studies.Tumour biopsies collected pre, during and post therapy (time of progression). If sufficient tissue is available, three biopsies will be obtained at each timepoint, and prioritized in the following order:FFPE tissue.Snap-frozen tumour biopsies.Fresh tumour cells/tumour infiltrating lymphocytes frozen as cell suspension (selected sites).A separate biopsy (snap-frozen) will be taken at week 6 from those patients who consent to the procedures.Blood samples collected pre-, during and post-therapy:Peripheral blood mononuclear cells, processed with gradient centrifugation and frozen on liquid nitrogen (selected sites).Plasma/serum, separated and frozen.Circulating tumour cells (only if sufficient resources available).Urine samples collected pre-, during and post-therapy.Faecal samples collected at baseline, tumour evaluation timepoints and progression.Dual-time PET analyses at baseline, 6 weeks, 1 year and at progression (selected sites).

